**Study Intervention**

Approximately 40 infants aged 2 to 3 months will be recruited for a 6-month study with the intervention starting at around 6 months of age – The NZ Ministry of Health and World Health Organisation recommended age for introducing complementary foods (ref).

The study will be conducted in two stages to enable completion within the tight timeframe. Thirty (30) of the recruited infants will be receive a dietary intervention based on a prebiotic food (candidate food) and 10 infants will receive a probiotic control known to show relevant immune benefit(s) and accepted as an ingredient in infant nutrition. These 10 infants will serve as a positive control to ensure that our study design and methods in principle can detect probiotic-related immune benefit. Envisaged probiotic controls are: *Bifidobacterium longum subspecies infantis (B. infantis)* (ref) and *Bifidobacterium animalis lactis (B. lactis)* (ref).

Researchers will supply the dietary intervention at no cost to the participant. The food will be given to the infants daily in appropriate amounts according to their age and stage of weaning. The amount of food given to the infant will not displace other foods of important nutrient composition in the infant’s diet. The infant will be introduced to the food with their first complementary foods and the food will be consumed daily for the 6-month period of the intervention.

Parents and guardians will be requested to have their infant consume the supplied candidate food or probiotic control each day for a total of 6 months (i.e. from when the child turns 6 months old until they turn 1 year of age). Adherence will be measured using information from a monthly questionnaire with parents or guardians on the average amount of candidate food consumed per day in the previous month.

Outcomes

Parents/guardians will complete daily records of illness through reporting the incidence, severity, and duration of the 9 signs of upper and lower respiratory tract and GI infections. This will be completed throughout the course of the study. Specific consent will be obtained to access medical records for infection-related GP visits, medication prescription and use, and hospitalisation events from 6 to 12 months of age. The infectious nature of the illness will be established by microbiological data, and/or the use of validated questionnaires.

Data Collection

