Data collection will be conducted in a clinical setting for baseline, when the child is 4-6 months (CF1), 9 months of age (CF3), and 12 months of age (CF6). Additionally, brief monthly questionnaires administered over the telephone or as a face-to-face interview will collect information on the dietary intervention adherence and recent health history.

**Questionnaires** (baseline, CF1, CF3, CF6)

From 4 to 6 months, brief monthly questionnaires will determine breastfeeding, formula feeding, and whether/what solids have been introduced. Brief exit interviews will determine participant burden and suggestions to improve engagement with the intervention.

**Anthropometry** (baseline, CF1, CF3, CF6):

Standardised anthropometric measurements will include weight and length. Measurements will be performed using calibrated age-appropriate instruments, including electronic scales and measurement mat with the children wearing light or no clothing. Measurement accuracy will be monitored by two parameters, the degree of refinement (recorded to 0.5 cm or 0.1 kg) and the degree of tolerance (measurement agreement between 1 cm and 0.1 kg). Three serial measurements from each infant will be calculated. Prior to the measurement of weight, infants will be required to have a nappy change if soiled.

**Diet** (CF1, CF3, CF6):

Adherence to the food targets will be determined by daily retrospective questionnaires, product counts, and photographs of food offered and waste. Dietary intake will be measured at CF1, CF3, and CF6 using 3-day weighed food records. Breast milk remains an important component of the diet during the age period in question, and has important impacts on both the GI microbiota and immune function. Breast milk volume will be measured. Infant formula can be captured directly by the diet record.

**Blood** (CF1 and completion):

Specific consent will be sought to collect two blood samples (CF1 and CF6). The blood sample will be collected by a trained phlebotomist and will be used to assess the following:

- The protective antibody response in plasma following the oral rotavirus which is administered in the standard immunisation schedule at 6 week, 3 months, and 5 months of age. (Isolauri 1995)
- The protective antibody response in plasma following the intramuscular pneumococcal vaccination which is administered at 6 weeks, 3 months, 5 months, and 15 months of age. (Bunout 2004, Perez, 2010)

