A plasma sample will be obtained for global metabolite profiling and total antibody titres in plasma will be assessed at 6, 9 and 12 months as a non-specific measure of protective antibody responses.

Peripheral blood mononuclear cells will be isolated to perform B cell receptor (BCR) repertoire analysis. The total antibody repertoire encoded by B cells is continuously shaped by exogenous as well as endogenous factors, such as vaccines [Galson 2014] and the GI microbiota [Wesemann 2015], both key variables in the study. The high-throughput analysis of the BCR repertoire, by means of next-generation deep sequencing of the immunoglobulin heavy chain complementary determining region (CDR) [Perez 2010], will provide the necessary depth of analysis to detect potential changes in the clonal diversity of individual antibody repertoires while changes to the microbiota are being made via the proposed nutritional intervention [Boyd 2016, Georgiou 2014].

**Urine** (baseline, CF1, CF3, and CF6)

Urine samples will be taken at collected at 6, 7.5, 9 and 12 months for global metabolite profiling. Clean catch urine samples are the recommended method for urine collection. If not available, other non-invasive methods such as the use of urine collection pads should be used (NICE Guidelines). Parents/caregivers will be provided with all necessary equipment for the successful collection and storage of urine samples. Collection pads for obtaining urine specimens from young children, such as the Euricol® Newcastle Urine Collector (UK). Sample collection will be as follows: parents/caregivers must ensure that the participating child’s genital area is clean and dry (using un-medicated products). The collection pad is applied to the area where urine is voided, i.e. in an infant, the pad can be kept in place with a disposable nappy fitted inside out (so that there is no potential for the nappy to absorb the urine). The pad should be checked every 10 minutes to see if it is wet. If no urine is collected after 30 minutes then a new pad should be applied. Following successful collection on the pad, a syringe should be used to draw urine up out of the pad. Samples should be transported to the clinic within a short time frame, or can be stored in a refrigerator and processed appropriately.

**Stools** (baseline, CF1, CF3, and CF6)

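### The written 4-6 month window for CF1 lets some of the only pre-feeding blood samples fall before the 5-month vaccine doses, and no rule places CF1 sampling before the first study food

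*Protocol*

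**What the plan says.** **Visit age.** Data Collection schedules the visits at baseline and then "when the child is 4-6 months (CF1), 9 months of age (CF3), and 12 months of age (CF6". Tables 1 and 2 repeat 4 to 6 months for CF1. The Blood section points to a later age: "total antibody titres in plasma will be assessed at 6, 9 and 12 months". The urine, stool and saliva sections also list 6 months as their earliest sampling age.

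**Blood.** "Specific consent will be sought to collect two blood samples (CF1 and CF6" are the only draws, and Table 1 marks venous blood at those two visits alone, as an opt-in. Plasma is to show the response to rotavirus vaccine, "administered in the standard immunisation schedule at 6 week, 3 months, and 5 months of age", and to pneumococcal vaccine, "administered at 6 weeks, 3 months, 5 months, and 15 months of age". Blood cells are used for BCR repertoire analysis, and the repertoire is described as "continuously shaped by exogenous as well as endogenous factors, such as vaccines" and the gut microbiota.

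**Start of study food.** Study Intervention gives two rules: "The infant will be introduced to the food with their first complementary foods", and daily use "from when the child turns 6 months old until they turn 1 year of age". The key to Figure 1 gives a third, with the intervention beginning at CF1. Participant characteristics expects first solids at around 6 months and not before 4.

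**Analysis.** Background, Sample Size and Data Analysis all treat each infant as its own control, compared before and after feeding.

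**The concern.** A within-infant comparison removes differences between infants. It does not remove other events that fall between the two samples in some infants and not in others. A vaccine dose is such an event, and here it acts directly on what is being measured. If dose status at CF1 varies, the CF1-to-CF6 change in vaccine antibody is not the same quantity in every infant. The BCR comparison is exposed for the reason the Protocol itself gives.

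Blood depends on CF1 in a way the other samples do not. Stool, urine and saliva are also collected at 2 to 3 months, whereas blood has no earlier draw. If an infant has eaten study food before CF1, there is no pre-feeding blood value and none can be recovered.

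What is at stake is the milestone on measuring vaccine response, which includes a judgement on whether the data are usable, and the objective of choosing outcomes for the later randomised trial.

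**Working it through.** There is no sample-size or power figure to reproduce, and the point does not depend on one. The check compares ages and dates.

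**1. Doses between the two blood samples.** Doses are due at 6 weeks, 3 months and 5 months (Blood section). By CF6 at 12 months, 3 of 3 are due.
- CF1 at 4 to under 5 months: 2 of 3 given, so 3 − 2 = 1 dose falls between CF1 and CF6.
- CF1 after the 5-month doses: 3 of 3 given, so 3 − 3 = 0 doses fall between.
- CF6 comes 12 − 5 = 7 months after the third dose. The 15-month pneumococcal dose comes after CF6 and plays no part.

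**2. Where Figure 1 puts CF1.** The five groups of 8 have baseline in Feb, Mar, Apr, May and Jun 2018, CF1 three calendar months later, and CF3 and CF6 at further three-month steps. Summing the groups gives 8, 8, 8, 16, 16, 8, 16, 16, 8, 16, 16, 8, 8, 8 for Feb-18 to Mar-19, which is the figure's own monthly row. A four-month gap from baseline to CF1 does not reproduce it.
- Counting back: CF1 to CF6 is six calendar months in every group (May to Nov, through Sep to Mar). With CF6 at 12 months, nominal CF1 is 12 − 6 = 6 months, or about 5 to 7 allowing a month either way for calendar rounding.
- Counting forward: baseline at 2 to 3 months plus 3 gives 5 to 6 months, or about 4 to 7 with the same allowance.

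The timeline therefore points to about 6 months, which agrees with the plasma ages and with feeding from 6 to 12 months. The window printed in Data Collection and Tables 1 and 2 is wider and still permits a draw before 5 months.

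**3. Order of blood and food.**
- Food starts on turning 6 months: blood in the 4-6 month window precedes it, provided a draw at 6 months comes before the first portion.
- Food starts at CF1: blood precedes it only if samples are taken first, which is not stated.
- Food starts with first solids: an infant weaned before its CF1 visit could already have eaten it. Data Collection foresees such weaning, since it asks monthly about solids from 4 to 6 months. Table 1 also marks the adherence questionnaire at CF1.

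**4. Illustration of size (assumed inputs).** Let p be the share of infants bled before the third dose. Let d be the difference in mean CF1-to-CF6 change between those infants and the rest, in SDs of change among infants of like dose status. The mean change shifts by p·d and its variance is multiplied by 1 + p(1 − p)d².

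| p | d | Shift in mean (SD) | Variance factor |
|---|---|---|---|
| 0.10 | 0.5 | 0.05 | 1 + 0.09 × 0.25 = 1.02 |
| 0.10 | 1 | 0.10 | 1 + 0.09 × 1 = 1.09 |
| 0.25 | 0.5 | 0.13 | 1 + 0.1875 × 0.25 = 1.05 |
| 0.25 | 1 | 0.25 | 1 + 0.1875 × 1 = 1.19 |

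For scale, the standard error of the mean change with all 30 fed infants is 1/√30 = 0.18 SD. Because blood is opt-in, the number with both samples may be smaller and the standard error larger. The Protocol gives neither p nor d.

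**The case against.** The best defence is that the Protocol already means 6 months. Figure 1's spacing, the 6-month sample ages and the 6-to-12-month feeding period agree, and 4 to 6 months can be read as an outer limit allowing for early weaning. The start rules can be reconciled too: CF1 is the start visit, researchers supply the food, and so none is eaten beforehand. This is also a non-randomised feasibility study. Its sample-size milestones for the full trial concern infection and microbiota, not antibody or BCR change, and one milestone already counts children who followed the immunisation schedule.

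Much of this stands, and it limits the size of the problem. It does not remove it. The wider window is the one printed in the visit schedule and both tables, and staff who follow it may draw blood before the dose. Nothing ties the draw to the dose or to the first portion. A percentage following the schedule does not show whether a given draw came before or after the dose. An analysis plan could adjust for dose status only if dates are kept, and would then be splitting at most 30 fed infants.

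Two stronger readings should be resisted. A reader might infer that half the CF1 bloods, (5 − 4)/(6 − 4) = 50% or 20 of 40, precede the dose. That assumes ages spread evenly over the window and vaccination on time, and it treats the outer window as the plan, against the evidence of Figure 1. A reader might also infer that early weaners will lose their pre-feeding blood. If food is first given at CF1 after sampling, none will; the documents show only that this is not guaranteed.

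**Conclusion.** The point holds as a badly fixed rule with limited reach. The written window allows CF1 blood on either side of the 5-month doses, so the CF1-to-CF6 antibody and BCR change can span one dose in some infants and none in others. The number affected cannot be derived; given the 6-month nominal age it is probably a minority, and opt-in consent reduces it further. On the assumed inputs above, the shift in mean change ranges from negligible to somewhat more than one standard error.

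Study food before CF1 sampling is a possibility that the start rules leave open, not an expected event.

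The point on dose timing is confined to the opt-in blood antibody and BCR outcomes, for which CF1 is the only candidate before-value. It leaves the consumption, consent, draw-success and recruitment counts intact. The change is worth making because a mixed before-value weakens the judgement on whether vaccine-response data are usable, and prevention is cheap.

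**What to change.** - In Data Collection and Tables 1 and 2, state CF1 as nominally 6 months, with CF1 blood drawn after the 5-month doses.
- In Study Intervention, state that study food is handed out only at CF1, after the CF1 samples are taken, and align the start rules with this.
- Record three dates: the 5-month doses, any earlier solids, and the first portion of study food.
- If an infant weans early and CF1 is brought forward, or the doses are late, do not withhold the food. Sample before the first portion, and flag that infant's antibody and BCR change or analyse it separately.

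The cost is a few text edits and three date fields, with no added visit or sample. The trade-off concerns early weaners. Holding the food until 6 months for everyone would keep dose status uniform where vaccination is on time, but those infants would no longer receive it as a first food. Bringing CF1 forward and flagging keeps the intervention as intended, at the price of a few antibody and BCR changes that must be set apart.

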**Multi-omics data generation and systems-level analysis**

The plasma and urine samples will be analysed using gas chromatography-mass-spectrometry (GC-MS) [Chan 2011] and liquid chromatography-mass spectrometry (LC-MS) methods [Fraser 2013a, Fraser 2012]. This global metabolite profiling methodology using a MS based approach monitors low molecular weight (<2000) polar and non-polar metabolites present in biological samples and generates data useful for characterising phenotypes, or determining levels of differentially expressed metabolites by treatments. Identification of significant metabolites will be performed by a combination of searching in-house and public mass spectral and metabolic pathway databases (HMDB, Metlin, MassBank, KEGG) to assist in component identification and interpretation of the function of the metabolites of interest, or if no library match is found, by performing more advanced MSn experiments to elucidate structural information [Fraser 2013b, Wishart 2013]. The team will have access to the most comprehensive Metabolomics Platform in NZ and Australia, i.e. at AgR.

Microbial function will be assessed by shotgun sequencing of metagenomic DNA [Young 2016] using the Illumina HiSeq platform in conjunction with microbial profiling by pyrotag sequencing of bacterial 16S rRNA gene amplicons. Microbial profiling of faecal samples (6, 7.5, 9 and 12 months of age) will be performed first and the data used to select at least two time points for the metagenomic analysis. Sequencing data will be analysed using bioinformatics tools such as Qiime [Caporaso 2010], MG-RAST [Meyer 2008], and IMG [Markowitz 2012]. While increasing the number of specific members of the microbiota is not considered in itself by EFSA a beneficial physiological effect [ESFA 2010)], CFDA has a pre-approved claim based on regulating GIT flora. Better understanding of the microbiota functionality is primordial to understand how the host and the microbiota interact in term of a food and health claim.

Randomisation

N/A

Blinding

Neither the participant nor researcher will be blinded.

Sample Size:

This feasibility study will determine the power for a subsequent RCT there no sample size calculations are required. The proposed sample size of 30 infants who will receive the feeding intervention and 10 infants will receive the active control (probiotic) for a period of 6 months. This sample target is based on an achievable recruitment rate of participants within a 12 month time frame and allows for follow up for 6 months.

In addition to classical case/control analyses, every infant will not only be sampled but also analysed before and after the prebiotic feeding, i.e. being assessed as a case/control pair, in addition to classical data analysis. This “personal” case/control pairwise analysis will account for differences in infant feeding before the actual intervention (e.g. duration of breast feeding, infant formula differences) and can be interpreted as a multiplexed n-of-1 trial.

The feasibility aspect of this study will assess compliance and rate of loss to follow up. This data will be used to inform a subsequent RCT. In previous studies and prevalence studies that we have conducted in 12 to 24 month old children the recruitment rate has been approximately 2 participants per week.

Statistical methods

A multiplexed n-of-1 clinical design trial design in which every infant is sampled before and after the intervention, and followed up. Thereby constituting its own case-control pair.

Data Management

Each participant will be assigned a trial identity code which will be allocated at enrolment to allow for link-anonymisation of data. The documents and database will also use infant date of birth. All personal data will be stored on an encrypted drive with links to personal information only being available to the study co-ordination team. Paper forms and hard copies will be stored in locked filing cabinets in secure sites. Data will be consolidated by each site using the REDCap (Research Electronic Data Capture) software (RW.ERROR - Unable to find reference:1572). This is a secure web application which is password protected and not accessible by third parties. REDCap will be managed at the University of Auckland. The investigator will also keep a screening log with details of all participants screened for the trial with their name, date of birth, NHI number, and trial number. The investigators will permit monitoring, audits, review, and regulatory inspections, providing direct access to source data/documents (where appropriate).

All measures and entered data are double-checked against source documents. Trained personnel will conduct the study according to standard operating procedures and protocols. All incidents or deviations from the protocol will be documented. A major violation is defined as one that may impact subject safety, affect integrity of the study data and/or subject’s willingness to participate in the study. This is a serious discrepancy resulting from error, fraud or misconduct e.g. failure to obtain informed consent or a breach in randomisation procedures. Should a major violation occur HDEC will be notified. Adverse events will be reviewed by an internal clinician; should any events be deemed as concerning for the health of the child they will make a decision as to whether the child’s GP needs notification (if consented to do so) or in more extreme cases, will withdraw the child from the study and make recommendations for clinical care. Should caregivers (parent or legal guardians) not wish to provide GP details, the clinician will contact them directly in situations deemed necessary in his medical opinion. All essential documents, including source documents will be retained for a minimum period of 10 years following the end of the study.

Data Analysis

Integrated analysis of the multi-omics data from multiple platforms will be performed to visualise and interpret changes according to biological pathways and networks. This will be performed using software tools such as Ingenuity Pathway Analysis (IPA), mixOmics [Le Cao 2009], and metaCyc [Caspi 2014]. In additional to classical case/control analyses, every infant will not only be sampled but also analysed before and after the “prebiotic” feeding, i.e. being assessed as a case/control pair, in addition to classical data analysis. This “personal” case/control pairwise analysis will account for differences in infant feeding before the actual intervention (e.g. duration of breast feeding, infant formula differences) and can be interpreted as a multiplexed n-of-1 trial [24].

Clinical Pilot Study Objectives and Milestones

1. To determine whether infants will consume the target food(s) in a dose estimated to be sufficient to impact protection against infection *via* modification of the microbiome and associated metabolite changes.
2. Milestone 1: Amount of the candidate food(s) free-living infants are offered and consumed over the complementary feeding period (6 to 12 months of age).
3. Milestone 2: Best method(s) to collect data on adherence to consuming the candidate foods (number attempted, number completed, quality).
4. To determine the feasibility of the outcome measurements (infection, immune, microbiome, host/microbe metabolome), assess recruitment potential, and identify high prevalence adverse events.
5. Milestone 1: Feasibility of measuring protection against infection using daily parental report of infection (number attempted, number completed, quality).
6. Milestone 2: Feasibility of measuring immune response to the rotavirus and pneumococcal vaccines in venepuncture blood and saliva as measures of immune function (% of children who followed the immunisation schedule, % of parents who agree to blood test, % successful blood draws in young children, data fit to purpose).
7. Milestone 3: Feasibility of using medical records as a measure of immune response
   (% of parents who agree to data access, completeness of data access, data fit to purpose).
8. Milestone 4: Feasibility and logistics of collecting 4 faecal samples between 6 and 12 months of age (number collected).
9. Milestone 5: Recruitment rate per month and extent and type of advertising required.
10. Milestone 6: Prevalence and nature of parent-reported adverse events, and identification of gross changes in growth rate.
11. To determine an appropriate sample size for the proposed full clinical trial.
    1. Milestone 1: Sample size required for the primary objective of the proposed clinical trial – improved immune protection from infection as a result of consuming the candidate food(s).
    2. Milestone 2: Sample size required for the secondary objective of the proposed clinical trial – altered microbiota as a result of consuming the candidate food(s).

Research Plan (2019 – 2024)

The present proposal aims at delivering the scientific insight and development concept to enable design and execution of a follow-up full clinical trial, informed by the pilot trial described in the present submission. The full-scale clinical study will test whether and how immune protection benefits can be conferred to infants around the weaning period by “targeted prebiotic feeding”. In contrast to the pilot trial (conducted at the Liggins Clinical Research Unit) this full trial is envisaged to be set up and performed at the “Starship Children's Health” Hospital, Auckland.

The full CT is conceived to have three arms: (i) one group of infants will receive a prebiotic feed as informed by our ECF developments (Tranche I); (ii) the second group will receive a control complementary feeding (“standard weaning food”) as recommended and accepted in today’s infant nutrition practice; (iii) the third (smaller) group of infants will be given a probiotic control, known to show relevant immune-protection benefit(s) and accepted as infant nutrition ingredient, as a positive control (like in in the pilot trial.)

We plan to extend the omics-based molecular phenotyping from microbiomics, metabonomics, BCR sequencing, and immune cell biology, to proteomics and beyond. This comprehensive molecular phenotype will be correlated with classical clinical readouts. As tested in the pilot CT, we will analyse the full CT data by both classical group comparisons and longitudinally, with every child being analysed individually, before and after the prebiotic complementary feeding. This latter analysis is expected to deliver microbial, immune and health trajectories across the weaning period.

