# **STUDY METHODS/DESIGN**

Ethical Considerations

Ethical approval will be obtained from The Northern B Health and Disability Ethics Committee (HDEC) of the Ministry of Health, New Zealand (HDEC reference number TBC).

Trial Design

Nourish to Flourish is a non-randomised clinical pilot study with an active control involving 40 infants (and mothers) which will examine the feasibility of conducting a randomised controlled clinical trial (RCT) to support immune protection against infection. This study will be conducted in Auckland, New Zealand. The study outline is shown in **Figure 1**.

Participant characteristics

Eligible study participants for the feasibility study are 40 healthy infants 2 to 3 months of age with the expectation that they will be introduced to their first complimentary foods around 6 months of age, and not before 4 months of age, as per the Ministry of Health Food and Nutrition Guidelines (Ref).

Infants will be ineligible for enrolment if they: were born <32 weeks’ gestation; have a developmental disability (i.e., autism, intellectual disability); an illness likely to influence their nutritional status (e.g., a chronic illness known to cause malabsorption, digestive or metabolic disorders); who have a doctor-diagnosed cow’s milk allergy; have health conditions that affect feeding; are undergoing treatment with antibiotics; are receiving a supplement with a pre- and/or probiotic; or whose parents written or spoken English comprehension is likely to make participation difficult for them. The decision to participate and written, informed consent will be obtained by the research team from parents/guardians on the child’s behalf. Infants who were born premature or small for gestational age will also be excluded as they may have special dietary requirements.

Infants will be recruited from urban central and greater areas of Auckland. Recruitment strategies include electronic and print advertising through The University of Auckland, community outreach campaigns including coffee groups, antenatal groups, local newspapers, and appropriate social media platforms.

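### The blanket statement that no researcher is blinded leaves assays, omics pre-processing and infection classification without arm masking, an avoidable but unquantifiable risk of assessor bias

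*Protocol*

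**What the plan says.** The Trial Design section describes a "non-randomised clinical pilot study with an active control involving 40 infants", and the Randomisation entry is marked not applicable. The Sample Size section gives the split as "30 infants who will receive the feeding intervention and 10 infants will receive the active control (probiotic"). The Blinding section is one sentence: "Neither the participant nor researcher will be blinded". It makes no exception for any role.

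Infection is measured in two steps under Outcomes. First, "Parents/guardians will complete daily records of illness through reporting the incidence, severity, and duration of the 9 signs" of respiratory and gastrointestinal infection. Second, "The infectious nature of the illness will be established by microbiological data, and/or the use of validated questionnaires". No person or group is named as making that second decision. The same section adds consented access to medical records for GP visits, prescriptions and hospital events.

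Under Data Management, "Each participant will be assigned a trial identity code which will be allocated at enrolment to allow for link-anonymisation of data", with "links to personal information only being available to the study co-ordination team". The same section says that documents and database also carry the infant's date of birth.

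The Study Intervention section gives the 10 probiotic infants a specific job: they are a positive control, meant to show that the design and methods can in principle detect an immune benefit. The Sample Size and Data Analysis sections plan conventional case/control analyses as well as before-and-after analysis of each infant.

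**The concern.** Open feeding is hard to avoid in this study. Open assessment is not, yet the protocol's sentence covers both. Three kinds of work after the parent's record or the sample collection involve choices that knowledge of arm could influence:

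- **Classing an episode as infectious.** The and/or construction does not fix what evidence each episode needs. Nothing prevents someone who knows the product from deciding.
- **Omics pre-processing.** Filtering, feature selection and batch decisions precede any comparison.
- **Sample handling and interpretation in the laboratory.**

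With no random allocation and no masking of families, masked assessment is one of the few remaining protections for a comparison between arms. The comparison most exposed is the positive-control check. If those who process the immune data know which infants received the probiotic, a positive result is weaker evidence that the methods work. The infection data also feed the sample size of the planned RCT, and a study meant to test the feasibility of outcome measurement would leave masked assessment untried.

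**Working it through.** The protocol states no figure on this point, so there is nothing to reproduce. The check sets its sections against one another and bounds what the numbers can say.

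**1. Does any section provide masking?** Blinding rules it out for researchers in general. Outcomes names sources of evidence for infection but no masked classifier. The multi-omics section describes platforms and software without mentioning masking. Data Management provides a code, which serves link-anonymisation; the restricted access concerns personal information, not arm. No section says that the code conceals arm.

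**2. Does the code supply masking as it stands?** Not as written. It is assigned per participant at enrolment. Date of birth stays on documents and in the database; with a collection date it gives the infant's age, and so the visit, and it could identify the infant to staff who know the family. The code can be used for arm masking, but some extra labelling is needed.

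**3. How much material is exposed?** With 40 infants and the four visits of Table 1:

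| Sample | Calculation | Maximum |
|---|---|---|
| Stool | 40 × 4 | 160 |
| Urine | 40 × 4 | 160 |
| Saliva, visits in Table 1 | 40 × 4 | 160 |
| Saliva, ages in the Saliva section (6, 9, 12 months) | 40 × 3 | 120 |
| Blood, opt-in | 40 × 2 | 80 |

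These are ceilings on samples handled. They do not measure bias.

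**4. Can the bias be sized?** No. If true rates are equal and a fraction x of one arm's infectious episodes is wrongly classed as non-infectious, the observed rate ratio is 1 − x. An assumed x of 10% to 20% gives 0.90 to 0.80. That only restates the assumption, since the protocol offers no value of x.

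**5. Would such a distortion be visible here?** Assume 2 to 5 episodes per infant (an assumption; the protocol gives no rate) and Poisson counts, with SE(log RR) = √(1/events in food arm + 1/events in probiotic arm).

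- 2 per infant: 60 and 20 events; √(1/60 + 1/20) = 0.26; 95% limits a factor of exp(1.96 × 0.26) ≈ 1.7 either way.
- 5 per infant: 150 and 50 events; √(1/150 + 1/50) = 0.16; 95% limits a factor of exp(1.96 × 0.16) ≈ 1.4 either way.

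Overdispersion would widen both. A ratio of 0.80 to 0.90 would lie within random error.

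**6. Is masking compatible with the rest of the plan?** Arm masking is. Masking visit throughout is not: the multi-omics section uses the 16S profiles to choose at least two time points for metagenomic analysis, so visit must be known at that stage.

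**The case against.** The strongest case against is that little of what the pilot must deliver depends on masking. The infection milestone counts daily reports attempted and completed and their quality. The immune milestone counts adherence to the immunisation schedule, consent and successful blood draws. Apart from fitness of the data for purpose, masking changes none of these. No efficacy test or success threshold is set. The planned RCT's main contrast is the prebiotic feed against standard weaning food, an arm the pilot lacks, so a distorted food-to-probiotic ratio would not pass directly into the sample size. All of this stands and limits the weight of the point.

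Also correct: antibody titres, mass spectrometry and sequencing are largely instrument-read, so the exposure lies in handling, batch order, filtering and interpretation. No human classifier of infection is named. Medical records give a source besides the parental diary. Non-random allocation is a larger threat to any between-arm reading.

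It can be argued further that laboratories may in practice not know the arm, and that masking belongs in operating procedures or an analysis plan not shown here. This does not remove the point. The protocol has not left the matter open: it has decided it, in a sentence with no exception, and a later masking rule would sit awkwardly against that text. If laboratories do work without arm labels, the sentence is inaccurate and should be corrected anyway.

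A reader might go further and infer that assessor bias actually enters the outcomes, that a false rate ratio of 0.80 to 0.90 is to be expected, or that the existing codes already make masking complete. The documents support none of these: they show an unguarded step, give no misclassification rate, and describe the code as a privacy measure.

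**Conclusion.** The point holds as a design choice with a better and inexpensive alternative. It rests on reading the word researcher without exceptions, as the protocol writes it, and on the absence of any masking provision elsewhere in it. The risk is greatest for the positive-control immune comparison, then for the conventional group comparisons, and is least direct for the infection data informing the RCT. Within the infection outcome, classification is the step most open to judgement.

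No size can be attached to the risk. Arm masking would not remove bias in what unblinded parents report, would not repair non-random allocation, and would leave most feasibility counts unchanged. This is worth correcting; it does not undermine the pilot's main purpose.

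**What to change.** Reword the Blinding section to say that:

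- parents and visit staff are not blinded;
- laboratory staff, those who pre-process omics data, and whoever decides that an illness episode is infectious work from coded samples or listings that show neither arm nor date of birth;
- one written infectious-illness rule, stating what evidence suffices, applies to both arms;
- the arm link is released once classification and pre-processing are locked.

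Do not require visit masking where visit is needed, such as the choice of metagenomic time points; that step should be masked to arm only.

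The cost is some extra label coding, a masked listing from REDCap prepared by the existing co-ordination team, and a short delay before laboratory data can be linked to arm. No extra assessor is needed, and the feeding design, sample size and burden on families do not change.
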